#### Postoperative findings

Postoperative assessments will focus on the presence of air leakage, duration of chest tube indwelling, and incidence of prolonged air leakage. Additionally, the need for chest tube reinsertion due to delayed air leakage following tube removal, the necessity of any further interventions, and the occurrence of any adverse events will be evaluated.

### Ethical aspects

The study will be conducted in accordance with the Declaration of Helsinki (revised in 2013).

This study has received ethical approval from the Chiba University Certified Clinical Research Review Board (CRB3180015) and has been registered with the Japan Registry of Clinical Trials (jRCT1032220620). The investigators will explain the concept of the trial to the patients and obtain written informed consent from each patients, including consent for the use of their data in study publications. The initial version of the protocol was approved on January 18th, 2023, and patient recruitment began in March 2023. The latest version 1.3, was approved on March 24th, 2024.

### Endpoints

The primary endpoint is the incidence of intraoperative stapler-related air leakage. Air leakage assessed in this study will be categorized as follows: stapler-related air leakage and air leakage not caused by the stapler. Stapler-related air leakage is defined as air leakage that is considered to have been caused by invasion with an automatic suturing device during pulmonary resection (e.g., staple holes, stamps, staple line overlapping sites, and pleural defects near the staple lines). Air leakage not caused by a stapler is defined as air leakage not caused by an automatic suturing device (e.g., pleural defects due to adhesion dissection and lung injury grasping during surgery).

The secondary endpoints are as follows: (1) time required to repair the intraoperative air leakage; (2) duration of postoperative chest tube placement; (3) use of additional procedures; (4) incidence of delayed air leakage; (5) incidence of intraoperative air leakage due to automatic suturing devices; (6) incidence of intraoperative air leakage, postoperative air leakage, and delayed air leakage during surgical procedures; and (7) number of automatic suturing devices used in pulmonary resection.

Other postoperative adverse outcomes will be confirmed as the safety endpoint.

The exploratory issues are as follows: (1) preoperative clinical diagnosis; (2) pathological diagnosis; (3) comorbidity; (4) intraoperative approach (video-assisted thoracic surgery (VATS), hybrid VATS, and open thoracotomy); (5) surgical duration (min); (6) method of the procedure if the procedure was performed for a persistent air leakage; (7) duration of postoperative hospital stay (days); (8) concomitant medications; (9) respiratory function tests; and (10) evaluation of emphysema by measuring the low attenuation volume in lung field analysis using 3D-CT images.

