## Abstract

**Background:**

Air leakage during pulmonary resection is a major complication in thoracic surgery. It frequently occurs at sites of adhesion dissection, due to lung manipulation, and along the staple lines of automatic suturing devices, particularly in cases of pulmonary fragility such as those of emphysema and interstitial pneumonia. Persistent postoperative air leakage prolongs chest tube indwelling and extends hospitalization time. Staplers with absorbable tissue reinforcements have been introduced for pulmonary resection to prevent intraoperative stapler-related air leakage. This phase II prospective, open-label, randomized, parallel-group trial aims to validate the efficacy of staplers with or without absorbable tissue reinforcements in controlling stapler-related air leakage during anatomical pulmonary resections.

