**Discussion:**

This trial will validate the effectiveness and safety of staple line reinforcements in controlling intraoperative air leakage during anatomical pulmonary resections, potentially leading to optimized strategies for patients with conditions such as emphysema and interstitial pneumonia.

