#### Sample size

A total of 120 patients will be recruited. The recruitment period extends from January 2023 to December 2025. The presence or absence of intraoperative air leakage in the staple line reinforcement and non-use groups will be investigated. Based on the results of a retrospective study conducted at our institution, the expected intraoperative air leakage rates in the staple line reinforcement group and group without staple line reinforcement are 27% and 50%, respectively. With a significance level of 5%, power of 70%, and a 1:1 allocation between the groups, 55 patients have been estimated to be required in each group. Considering ineligible cases and dropouts, the enrollment of 60 patients in each group has been planned.

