### Procedure

#### Intraoperative findings

Factors such as background lung (presence of emphysema or interstitial pneumonia), presence of adhesions, operative time, blood loss, presence of interoperative air leakage, and time to repair pulmonary air leakage, will be assessed. Surgical cases in which the use of an automatic suturing device is judged to be not required for pulmonary resection and those considered unsuitable for en bloc resection were considered ineligible.

After pulmonary resection, a standard water-seal test will be conducted, beginning at an airway pressure of 15 cm H₂O and progressing to a maximum pressure of 20 cm H₂O. The presence, location, and extent of air leakage due to intraoperative manipulation, such as that at the staple line site, will be assessed. If air leakage is observed, its location and extent will be documented and the time required for repair (in minutes) will be recorded.

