### Statistical analysis

For the primary endpoint, proportions were calculated and comparisons between groups were performed using the chi-square test. To supplement the analysis of the primary endpoints, we also analyzed the secondary endpoints. No multiplicity adjustments were made in the analysis of secondary endpoints. For each secondary endpoint, group comparisons were conducted using a *t* test for continuous variables and the chi-square test or Fisher's exact test for categorical variables.

The safety endpoint was the frequency of adverse events; we recorded the frequency and proportion of adverse events, created a list of these, and calculated the frequency. All comparisons were planned and all *p* values were two sided. Statistical significance was set at *P* < 0.05. All statistical analyses were performed using the SAS software (version 9.4; SAS).

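### The primary comparison is an unadjusted chi-square test, although the protocol names lung fragility as a driver of leakage and plans a CT measure of it: a modest, recoverable loss of efficiency

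*Protocol article*

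**What the plan says.** All references are to the protocol article.

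- **Fragility as a driver.** The abstract's Background says leaks occur at staple lines and elsewhere, "particularly in cases of pulmonary fragility such as those of emphysema and interstitial pneumonia". The closing Discussion again names emphysema, smoking and background lung fragility.
- **Allocation.** Under Participants and randomization, sex and procedure are the allocation factors. Sex is chosen partly because it travels with respiratory function, smoking and frailty, so it serves as an indirect proxy for fragility.
- **Measurement.** Table 1 marks spirometry and chest CT at enrolment only. Endpoints places respiratory function tests and "evaluation of emphysema by measuring the low attenuation volume in lung field analysis using 3D-CT images" among the exploratory issues.
- **Primary analysis.** Under Statistical analysis, proportions are calculated and "comparisons between groups were performed using the chi-square test". No covariate or stratification is named, so the allocation factors are not carried forward either.
- **Intraoperative record.** Intraoperative findings begins its list of items to be assessed with "Factors such as background lung (presence of emphysema or interstitial pneumonia". No analysis is attached to that record.
- **Hoped-for use.** The abstract's Discussion describes the trial as "potentially leading to optimized strategies for patients with conditions such as emphysema and interstitial pneumonia".

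**The concern.** A baseline variable that predicts the outcome can be put to work at almost no cost. Adjusting for it sharpens the treatment comparison and protects the estimate against chance imbalance in that variable. This trial plans its power at only 70%, so recoverable power is worth having. The article identifies fragility as relevant and balances a proxy for it through sex. It plans a direct CT measure but gives that measure no part in the primary comparison.

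The article is not silent on the primary method, which would leave the matter to an analysis plan. It names the unadjusted test. What is at stake is a few points of power and a less robust estimate, not the validity of the result.

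**Working it through.** **Inputs from the article**
- Sample size: "With a significance level of 5%, power of 70%, and a 1:1 allocation between the groups". The expected leakage rates with and without reinforcement "are 27% and 50%, respectively". The stated need is 55 per group, with 60 enrolled.
- Statistical analysis: all p "values were two sided".
- Strength of the fragility–leakage association: not given. Odds ratios (OR) of 1.0, 1.5, 2 and 3 per SD are assumed below.

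**Step 1. Reproduce the sample size**

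Pooled-variance formula for two proportions, with mean rate (0.27 + 0.50)/2 = 0.385:

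n = [1.960 × √(2 × 0.385 × 0.615) + 0.524 × √(0.27 × 0.73 + 0.50 × 0.50)]² / 0.23²

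= [1.960 × 0.688 + 0.524 × 0.669]² / 0.0529 ≈ 54.6, so 55 per group.

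The article's figure reproduces and matches an uncorrected, unadjusted chi-square test. The same formula gives power of 70.3% at 55 per arm and 74.1% at 60 per arm.

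**Step 2. Fragility covariate alone**

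Simulation with 5,000 replicates per scenario (Monte Carlo standard error about 0.6 points), a standard-normal covariate and marginal rates held at 27% and 50%. The comparison is between the unadjusted test of proportions and logistic regression on arm and covariate, at 55 per arm:

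| Assumed OR per SD | Unadjusted | Adjusted | Difference (points) |
|---|---|---|---|
| 1.0 | 72.4% | 71.2% | −1.2 |
| 1.5 | 71.5% | 72.2% | +0.7 |
| 2 | 71.5% | 74.6% | +3.1 |
| 3 | 70.2% | 77.9% | +7.7 |

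Type I error was about 4% to 5.6% for both tests over all scenarios run, at 55 and at 60 per arm.

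To put this on the scale of patients: going from 55 to 60 per arm adds 74.1 − 70.3 = 3.8 points. The 3.1 points at OR 2 are therefore worth about 5 × 3.1/3.8 ≈ 4 patients per arm.

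**Step 3. Fragility covariate with sex and procedure**

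A further simulation, also at 55 per arm and 27% versus 50%, used a logistic model with arm, sex, procedure and the continuous covariate. Unadjusted power was about 70–72%. Adjusted power was 72%, 72.5%, 75.6% and 78.6% at OR 1, 1.5, 2 and 3 per SD, with type I error of 4.5–5.1%.

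**Step 4. A binary emphysema factor**

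Assumed: 35% prevalence, OR 2 each for sex and for procedure, 55 per arm, 8,000 replicates.

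| Emphysema OR | Chi-square | CMH by sex and procedure | CMH also by emphysema |
|---|---|---|---|
| 2 | 70.2% | 71.5% | 71.0% |
| 4 | 70.4% | 71.7% | 73.9% |
| 5 | 71.2% | 72.3% | 76.1% |

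Sex and procedure alone add 1.1 to 1.3 points here. The part due to emphysema is −0.5, +2.2 and +3.8 points.

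**Step 5. Chance imbalance**

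Under simple randomisation with 55 per arm:
- Continuous measure: the SD of the between-arm difference is √(2/55) = 0.191 SD, so the chance of a gap above 0.3 SD is about 12%.
- Emphysema at an assumed 30% prevalence: the SD is √(2 × 0.3 × 0.7/55) = 0.087, so the chance of a gap of 15 points or more is about 9%.

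**The case against.** The strongest reply is that this is a permissible choice, not a fault. The unadjusted test is valid under randomisation, its error rate already allows for chance imbalance, and it is the test for which the trial was sized. All of that stands. A reader might infer that the primary result would be biased or the sample size wrong. Neither follows, because Step 1 reproduces the size.

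Four other stronger readings are tempting, and the article supports none of them:
- **A marked emphysema imbalance is to be expected.** Step 5 puts the chance at about 9–12%. That is plausible, not likely.
- **A strong predictor is being ignored.** The article names fragility only qualitatively and gives no odds ratio or prevalence. With a weak covariate the gain is a point or less.
- **The abstract promises a conclusion for emphysema or interstitial pneumonia.** "potentially leading to optimized strategies for patients with conditions such as emphysema and interstitial pneumonia" voices a hope, so no formal subgroup analysis is owed.
- **The plan adjusts for a judgement made with the device known.** The trial is open-label and background lung is listed under intraoperative findings, but no stated analysis uses that record. It is only a caution for anyone who adds a covariate.

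Model size is a fair objection. Expected events are 55 × 0.27 + 55 × 0.50 ≈ 42. Four terms (arm, sex, procedure, low attenuation volume) leave about 10.6 events per term, and a fifth would leave about 8.5. This argues for a short model. The four-term form kept its type I error in Step 3.

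It can also be said that an unseen analysis plan may add adjusted analyses. It may, but the primary method stated here is the unadjusted test.

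**Conclusion.** The point holds as one of efficiency and robustness. The article names fragility as a driver of leakage and plans a CT measure of it, then fixes a primary comparison that does not use it.

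At 55 per arm, adjusting for sex, procedure and a continuous fragility covariate takes power from about 70–72% to roughly 72–73%, 75–76% or 78–79% at an OR per SD of 1.5, 2 or 3. There is essentially no change if the covariate is irrelevant, and type I error stays near 5%.

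The size rests on three assumptions:
- the odds ratio per SD, which the article does not give;
- the planning rates of 27% and 50%;
- the low attenuation volume coming from the enrolment scan, which follows from Table 1 but is not spelled out under Endpoints.

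The power figures are for the test of the arm term in the logistic model; power for the standardised risk difference was not simulated separately.

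**What to change.** Before analysis, prespecify a logistic model for stapler-related leakage with arm, sex, planned procedure and preoperative CT low attenuation volume as a continuous term. Report the standardised risk difference with its 95% CI as the adjusted estimate, beside the simple comparison of proportions. State that low attenuation volume is taken from the enrolment CT.

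Add interstitial pneumonia only if it is read from that same scan. The article lists no preoperative CT variable for it, and the intraoperative background-lung record should not stand in for one. An arm-by-low-attenuation-volume estimate with a CI is optional and should be labelled descriptive, since the trial is too small for more.

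The cost is a few sentences and a little programming. The scan is already scheduled and its low attenuation volume reading already planned. The small downside is that a model-based estimate will stand alongside the simple one.

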### Statistical analysis

For the primary endpoint, proportions were calculated and comparisons between groups were performed using the chi-square test. To supplement the analysis of the primary endpoints, we also analyzed the secondary endpoints. No multiplicity adjustments were made in the analysis of secondary endpoints. For each secondary endpoint, group comparisons were conducted using a *t* test for continuous variables and the chi-square test or Fisher's exact test for categorical variables.

The safety endpoint was the frequency of adverse events; we recorded the frequency and proportion of adverse events, created a list of these, and calculated the frequency. All comparisons were planned and all *p* values were two sided. Statistical significance was set at *P* < 0.05. All statistical analyses were performed using the SAS software (version 9.4; SAS).

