#### Participants and randomization

The patients will be enrolled before surgery and randomly allocated to four groups. The allocation process is based on the use of an automatic suturing device equipped with staple line reinforcements (absorbable tissue reinforcement composed of polyglycolic acid or glycolic acid–lactic acid polyester) versus a conventional automatic suturing device. Sex and procedure (lobectomy or segmentectomy) will be used for allocation to the following four groups: These factors have been selected because factors confounding sex such as respiratory function, smoking history, and general frailty, may influence lung fragility, and the number of automatic suturing devices planned for use may differ according to the procedure. Random allocation will be performed at a 1:1 ratio, with central registration at an independent data center, to minimize selection bias. The schematic of the study is shown in Fig. 1. Allocation for groups A and B will be achieved based on the aforementioned factors, whereas that for subgroups A1, A2, B1, and B2 was random and equal. The following devices were used in the groups:

Group A: Automatic suturing device with staple line reinforcement;

Subgroup A1: Powered ECHELON FLEX as the automatic suturing device, Tri-Staple cartridge, and ECHELON ENDOPATH^®^ Staple Line Reinforcement (ECHICON Johnson & Johnson, NY, U.S.A.) used for absorbable tissue reinforcement;

Subgroup A2: Signia Stapling System as the automatic suturing device and Tri-Staple 2.0 Reinforced Reload^®^ (Medtronic, Dublin, Ireland) used for absorbable tissue reinforcement;

Group B: Conventional automatic suturing device;

Subgroup B1: Powered ECHELON FLEX as automatic suturing device and Tri-Staple cartridge; and

Subgroup B2: Signia Stapling System as the automatic suturing device and Tri-Staple2.0.

The appropriate stapler size will be selected by the surgeon, based on the thickness and rigidity of the lung tissue to be resected.

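### Groups A and B are allocated on sex and procedure, but the stated primary test is an unstratified chi-square; if these factors predict leakage, it is mildly conservative and forgoes some power

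*Protocol article*

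**What the plan says.** Under Participants and randomization, the protocol article names two allocation factors: "Sex and procedure (lobectomy or segmentectomy) will be used for allocation to the following four groups". The mention of four groups is muddled, because the devices also form four subgroups (A1, A2, B1, B2). A later sentence in the same section makes clear that sex and procedure govern the main comparison: "Allocation for groups A and B will be achieved based on the aforementioned factors". The reasons given are that characteristics associated with sex may affect how fragile the lung is, and that the number of staplers may differ between lobectomy and segmentectomy. The Discussion adds that the procedure performed, together with respiratory function and smoking history, may help to predict intraoperative leakage.

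Under Statistical analysis, the primary test is fixed: "For the primary endpoint, proportions were calculated and comparisons between groups were performed using the chi-square test". Neither stratification nor adjustment is mentioned. Under Sample size, the planning basis is "With a significance level of 5%, power of 70%, and a 1:1 allocation between the groups", with assumed leakage rates of 27% and 50%, 55 patients required per group and 60 to be enrolled.

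**The concern.** Forcing balance on a prognostic factor removes chance imbalance in that factor from the treatment comparison. The true variance of the difference in proportions is then smaller than in an unrestricted 1:1 trial. A plain chi-square still estimates the larger, unrestricted variance. Its type I error drifts below 5%, and it rejects less often than a test that uses the strata.

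Efficiency is what is at stake, not validity. The trial accepts a 30% chance of missing its assumed effect, so power available without extra patients is worth having. The factors are recorded for allocation in any case. This is also not a detail left to an unseen analysis plan, because the article names the primary test and that test does not use the factors.

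**Working it through.** **1. The plan's own sample size.** Inputs from Sample size and Statistical analysis: rates 0.50 and 0.27 (difference 0.23, mean 0.385), alpha 0.05 two-sided, power 70%, 1:1 allocation. The uncorrected, unstratified formula is

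n = [z(0.975)·√(2·p̄·(1−p̄)) + z(0.70)·√(p₁(1−p₁)+p₂(1−p₂))]² / (p₁−p₂)²

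- First term: 1.960 × √(2 × 0.385 × 0.615) = 1.349
- Second term: 0.524 × √(0.2500 + 0.1971) = 0.351
- n = (1.349 + 0.351)² / 0.0529 = 54.6, rounded up to **55**, which is the stated figure.

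The same formula gives 70.3% power at 55 per group and 74.1% at 60. The planned 70% is therefore already the power of the unstratified test.

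**2. Why balance makes the plain test conservative.** Assumed, because the documents give no figures: a 60/40 split on sex, a 65/35 split on procedure, and the same odds ratio for leakage for each factor. At 60 per group, the four strata hold 8, 16, 13 and 23 patients per group. With odds ratio 3 per factor and an overall null rate of 50%, the stratum rates are about 0.20, 0.43, 0.43 and 0.69. The mean within-stratum variance is

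(8×0.160 + 16×0.245 + 13×0.245 + 23×0.214)/60 ≈ 0.222

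The plain test uses 0.50 × 0.50 = 0.250. The ratio is 0.222/0.250 = 0.89, so the plain test overstates the variance by about one eighth. At odds ratio 2 the same sum gives 0.237 (ratio 0.95), and at 4 it gives 0.208 (ratio 0.83).

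**3. Size of the effect.** Simulation with 200,000 trials per scenario. Groups are exactly balanced within strata, marginal rates are held at 50% and 27%, and the null rate is 50%. CMH is the Cochran-Mantel-Haenszel test over the four strata.

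| Per group | OR sex / procedure | Power chi-square | Power CMH | Difference (points) | Type I chi-square | Type I CMH |
|---|---|---|---|---|---|---|
| 60 | 1 / 1 | 74.6% | 74.4% | −0.2 | 5.5% | 5.5% |
| 60 | 1.5 / 1.5 | 74.6% | 74.8% | +0.2 | 5.3% | 5.3% |
| 60 | 2 / 2 | 74.7% | 75.7% | +1.0 | 4.9% | 5.0% |
| 60 | 3 / 3 | 75.6% | 78.7% | +3.1 | 4.1% | 4.9% |
| 60 | 4 / 4 | 75.9% | 80.7% | +4.8 | 3.5% | 4.9% |
| 55 | 1 / 1 | 71.1% | 70.1% | −1.0 | 4.6% | 4.6% |
| 55 | 2 / 2 | 71.3% | 72.8% | +1.5 | 4.0% | 4.9% |
| 55 | 3 / 3 | 72.2% | 75.5% | +3.3 | 3.3% | 5.1% |
| 55 | 4 / 4 | 72.5% | 77.3% | +4.8 | 2.7% | 5.0% |

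A second simulation used permuted blocks of 4 within strata (block size also assumed), 40,000 replicates and 60 per group. Power for chi-square versus CMH was 74.5% vs 74.3% at odds ratio 1, 74.8% vs 76.0% at 2, 76.2% vs 79.1% at 3, and 76.3% vs 80.9% at 4. The plain test's type I error was 3.6% at 4.

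**4. Reading the type I figures.** With no prognostic effect and a 50% null rate, the exact size of the plain chi-square is 4.5% at 55 per group and 5.5% at 60, from discreteness alone. Low values at 55 therefore cannot be put down wholly to the ignored strata. The comparison with CMH in the same row is the fair one.

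**The case against.** The strongest case against is that nothing here is invalid. A slightly conservative test cannot inflate false positives, the unadjusted risk difference is unbiased under 1:1 randomisation, and the sample size was computed for the very test that is stated. The prognostic strengths are assumed. The protocol says only that sex-related characteristics may matter and that stapler number may differ by procedure; it does not say that stapler number changes leak risk. For odds ratios up to 2 on both factors, the gain at 60 per group is about a point at most. All of this stands, and it limits the point to one of efficiency.

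Three stronger readings are tempting, and the documents do not support them:

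- A reader might infer that the test is certainly conservative. It is so only if the factors are prognostic.
- A reader might infer that the trial falls short of its 70%. It does not: 55 per group reproduces exactly from the unstratified formula, and enrolling 60 leaves room above it.
- A reader might infer that stapler platform must also enter the primary analysis. The article describes subgroup allocation as random and equal and gives no platform effect. Supportive models and interactions are commonly left to an analysis plan, which is not shown.

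What survives is the asymmetry. Stratifying costs about 0.2 points (60 per group) to 1 point (55 per group) if the factors are irrelevant, and gains up to about 5 points if they are strong.

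**Conclusion.** The point holds in conditional form: the stated primary test does not use the factors on which groups A and B are allocated. Whether that matters depends on how strongly sex and procedure predict leakage, and that cannot be read from the documents. Over odds ratios of 1 to 4 per factor, the consequence runs from none to a loss of about 5 points of optional power, with a modest fall in type I error that becomes clear only at the strong end. The sizes rest on the assumed stratum shares, near-exact balance within strata, and the protocol's own rates of 27% and 50%. This is a worthwhile, nearly free improvement and not a defect that threatens the trial's conclusion.

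**What to change.** Before the comparative analysis, amend Statistical analysis (or the analysis plan) so that the primary test is a Cochran-Mantel-Haenszel test stratified by sex and by planned procedure, each as entered at randomisation. Report the Mantel-Haenszel risk difference with a 95% confidence interval, and keep the unadjusted chi-square as a sensitivity analysis.

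The cost is a sentence or two of text. It needs no new data, patients or procedures, and the sample size can stay as it is.
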